## Abstract

*Background*: Up to 80% of patients who develop coronavirus disease-2019 (Covid-19) infection subsequently experience long covid/post-covid syndrome. The World Health Organization (WHO) has estimated that >770 million patients have been infected with Covid-19 globally. Even if only 10% of these patients develop long covid, > 75 million patients will suffer for a long period. Among the various symptoms of post-covid syndrome, fatigue is common, affecting up to 60% of the patients. As observed in other viral infections, elevated levels of inflammatory cytokines may play a role. Transcutaneous auricular vagal nerve stimulation (taVNS) is a noninvasive method that modulates the immune system via the central nervous system and has shown promising effects in autoimmune diseases and improving fatigue. In this pilot study, we investigated the feasibility of daily taVNS in patients with long covid-related fatigue. Additionally, the effects of taVNS on fatigue and quality of life will be analyzed. *Methods*: A total of 45 adult patients with long covid associated fatigue syndrome will be enrolled in this study, and will be randomized to the above-threshold-stimulation, below-threshold-stimulation, or sham-stimulation arms, after being informed that they will feel the stimulation. The above-threshold-group will receive a 4-week-long left-sided cymba conchae taVNS with 25 Hz, 250 µs pulse width 28s/32s on/off paradigm for 4 h throughout the day. The below-threshold group will receive stimulation below the sensational threshold, whereas the sham group will receive no stimulation following application of a non-functional electrode. The daily stimulation protocol will be recorded either manually or using the provided app. Three well-established questionnaires, the Multidimensional-Fatigue-Inventory-20, Short-Form-36, and Beck-Depression-Inventory, and the newly established Post-Covid-Syndrome-Score will be completed both before and after 4 weeks of stimulation. *Discussion*: The primary endpoint has been set as the patients’ average daily stimulation time after 4 weeks, while secondary endpoints include the effects of taVNS on fatigue and Quality of Live (QoL). As a non-invasive treatment option, taVNS may be a notable alternative for patients with post-covid related fatigue. *Trial registration*: This study was approved by the local ethics committee (23/7798) and registered (DRKS00031974) (see supporting information files). *Ethics & Dissemination:* The ethical justifiability of this study was supported by prior research demonstrating the safety of taVNS. Patients will be recruited by general practitioners, and written informed consent will be obtained. All data will be pseudonymized for collection and storage. The study results will be published in peer-reviewed journals with the aim of providing evidence of the potential of taVNS in long covid management. The study will be conducted in accordance with the principles of the Declaration of Helsinki.

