### Sample size calculation

The group size was based on the aforementioned studies on taVNS in other forms of fatigue [31,35,41], our aforementioned FatiVa study [42], and an ongoing similar study in the USA which enrolled 40 patients (NCT05630040). Recommendations for group size made in previous pilot studies were also considered [51,52]. Based on the expectation of the superiority of the two target groups (low- and high-threshold stimulation) of at least 5 and 10 MFI units, respectively, compared to the placebo (shift), and a type I error of alpha = 0.05, a total of 3 × 12 cases = 36 cases were deemed to be required to achieve a study power of 80% for the most important secondary endpoint, the MFI20 questionnaire. The mentioned numbers were secured with a safety margin of approximately 10%–20% (depending on the dropout rate), resulting in a total of 3 × 15 cases = 45 cases, if necessary. The calculation will be performed using the R Package “MultNonParam” [53].

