### Data analysis

The two-sided p-value of Fisher’s exact test will be used to evaluate the difference between the three groups (primary outcome is an incidence rate with patients who exceed a usage-time-threshold). Additionally, the two treatment groups will be descriptively compared with the placebo group, and between themselves. The rationale to use Fisher’s exact test is to compare binary data between groups (in total three two-group comparisons). The rationale for the Kruskal-Wallis rank analysis of variance is to avoid the potential influence of outliers and to handle unknown data distributions (normally distributed data are not expected).

Since three tests (each group compared with each other) are performed and the threshold for the p-value was set at an overall (studywise) alpha of 0.05, then three tests result in an Bonferroni-adjusted (comparisonwise) threshold of p/ 3 = 0.017. p-values below this threshold denote a statistical significant difference.

Secondary outcome measures included the MFI20, BDI, SF-36, and PCS-score, which were modified similarly to the primary outcome measures. BDI, SF36 and PCSS are other secondary measures which will be analyzed descriptively. Since those parameters are continous rank-analses of variance (Kruskal wallis tests) will be used. Descriptive statistics, such as means, medians, quantiles, and respective case numbers of the available data, will be reported. The between-group contrast will be reported as the mean difference with 95% confidence intervals. Additionally, a nonparametric estimation of the group effect (shift) using the Hodges-Lehmann estimator shift will be provided.

Successful acceptance and compliance will be defined as achieved when the acceptance criteria (average taVNS for 4 h/day) are met by at least 80% of patients. A total of 45 patients will be enrolled, with 15 assigned to each of the three groups: “sham”, “Verum-1”, and “Verum-2.” The decision to have 15 patients per group was based on feasibility, as well as from influence by studies that examined noninvasive VNS for sleep deprivation, lupus, and Sjoegren’s syndrome. Furthermore, the selected sample size was aligned with the recommended sample sizes for feasibility studies [51,52].

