#### Visit 0.

During the initial visit, patients will receive informational documents, sign informed consent forms, and complete the questionnaires. Personal data such as age, sex, height, weight, therapy time, duration, and type will also be documented. The patients will receive the stimulator and be instructed regarding its use by the investigator, according to the guidelines of the German Medical Devices Act (MPG/MPDG). Additionally, group assignment (SHAM, Verum 1, or Verum 2) will be performed. Subsequently, the 4-week stimulation phase will be initiated.

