#### Telephone interview after 7 days.

After 7 days, patients will be contacted by phone or email (if preferred) to inquire about their use of the stimulator, any side effects, or any potential questions they may have.

##### Visit 1

After 4 weeks, the patients will complete the questionnaires again. Personal data, including weight, will be collected, while data regarding the duration of stimulation will be retrieved from a smartphone. Subsequently, the stimulators will be returned. Patients who cannot attend visit 1 because of their health conditions will receive online access to the questionnaire section of the eCRF to complete it from home.

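### The Kruskal-Wallis analysis of the questionnaires is valid but takes no baseline covariate; adjusting for baseline would usually make the MFI20 comparison more precise, at a cost of about one point of power at worst

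*Protocol article*

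**What the plan says.** The Abstract says of the four questionnaires (MFI20, SF-36, BDI and the PCS score) that they "will be completed both before and after 4 weeks of stimulation". The Study procedure agrees: at Visit 0 patients "sign informed consent forms, and complete the questionnaires", and at Visit 1 "After 4 weeks, the patients will complete the questionnaires again". A baseline value is therefore planned for every questionnaire outcome.

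The Data analysis section names the test: "Since those parameters are continous rank-analses of variance (Kruskal wallis tests) will be used". It justifies ranks by possible outliers and unknown distributions. For estimation it says "The between-group contrast will be reported as the mean difference with 95% confidence intervals", and it adds a Hodges-Lehmann shift. No covariate is named. The section does not say whether the ranked quantity is the week-4 score or the change from baseline.

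The sentence naming the test directly follows "BDI, SF36 and PCSS are other secondary measures which will be analyzed descriptively". MFI20 is reached through the list just before it ("Secondary outcome measures included the MFI20, BDI, SF-36, and PCS-score, which were modified similarly to the primary outcome measures"), through the general rationale for Kruskal-Wallis in the same section, and through the Sample size calculation. That calculation plans MFI20 as a shift with a nonparametric R package. No other test is named for MFI20.

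**The concern.** A Kruskal-Wallis test cannot take a covariate. If week-4 scores are ranked, the baseline is not used at all. If changes are ranked, the baseline is used with a fixed weight of one, which adds noise when baseline and follow-up are only weakly correlated. Regression on baseline estimates the weight from the data.

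This matters most for MFI20. It is the leading secondary endpoint and the only one with a power target. The article also intends the fatigue results to inform whether later trials keep a suprathreshold arm (Study plan; Sham intervention).

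Arms are small, so chance baseline gaps are not small beside the 5-unit shift expected for subthreshold stimulation. If the baseline SD is about 7.3 (an assumption, see working), the standard error of a baseline difference between two arms is 7.3 × √(2/12) ≈ 3.0 units, or 7.3 × √(2/15) ≈ 2.7 with 15 per arm. A week-4 comparison carries the correlated share of such a gap into the estimate. This costs precision; it does not bias a randomised comparison.

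**Working it through.** **Inputs from the article (Sample size calculation).** Shifts of 0, 5 and 10 MFI units (sham, subthreshold, suprathreshold); alpha 0.05; 80% power; 3 × 12 = 36, raised to 3 × 15 = 45.

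**Inputs not in the article (assumed).** The MFI20 SD; the baseline to week-4 correlation ρ; normal data; equal SD at both visits.

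**Step 1. The plan's own figure.** Without an SD, 36 can be neither confirmed nor refuted, only solved backwards. The asymptotic Kruskal-Wallis noncentrality is λ = n × Σ(shift − mean shift)² / SD² × 3/π, with Σ = 25 + 0 + 25 = 50. Setting n = 12 and power 80% on 2 df gives SD ≈ 7.7. Simulation at 12 per arm (40,000 runs) gives 80.7% at SD 7.2, 79.5% at 7.3 and 78.5% at 7.4, so the implied SD is about 7.3. The inflation to 45 reproduces at 20% dropout: 36 / 0.80 = 45.

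**Step 2. Why adjustment should help.** For unranked scores with SD σ at each visit, the variance that drives the group comparison is:

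- week-4 score: σ²
- change score: 2σ²(1 − ρ)
- baseline-adjusted: σ²(1 − ρ²)

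In units of σ², these are 1, 1.40 and 0.91 at ρ = 0.3; 1, 1.00 and 0.75 at 0.5; 1, 0.60 and 0.51 at 0.7; and 1, 0.40 and 0.36 at 0.8. The change score does worse than the week-4 score when ρ is below 0.5. The adjusted analysis is never worse than either before ranking. The ranked version can fall slightly short, so it was simulated.

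**Step 3. Power of the three-group test at alpha 0.05, 12 per arm, SD 7.3 at each visit.**

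| ρ | KW, week-4 score | KW, change score | Rank ANCOVA (Quade) |
|---|---|---|---|
| 0.3 | about 80% | 64% | 82% |
| 0.5 | about 80% | 80% | 89% |
| 0.7 | about 80% | 96% | 97% |

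At ρ = 0, rank ANCOVA and week-4 Kruskal-Wallis are level to within half a point. At ρ = 0.8 (run at SD 7.4), change-score Kruskal-Wallis has 99.4% and rank ANCOVA 99.1%. Type I error is about 5% for all three methods.

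**Step 4. If 7.3 is the SD of the change.** The SD at each visit is then 7.3 / √(2(1 − ρ)). Change-score Kruskal-Wallis stays near 80% at every ρ. Rank ANCOVA gives 93%, 89%, 82% and 79% at ρ = 0.3, 0.5, 0.7 and 0.8.

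**Step 5. A larger SD.** At SD 12 with 15 per arm, week-4 Kruskal-Wallis has 46% power. Rank ANCOVA has 50%, 57% and 73% at ρ = 0.3, 0.5 and 0.7.

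**The case against.** The strongest reply is that nothing here is an error. Under randomisation Kruskal-Wallis holds its level on either outcome and the raw mean difference is unbiased. The article also gives a reason for using ranks. All of that stands. A reader might infer that the planned analysis is biased or invalid, and the document does not support that.

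A reader might also infer that the plan ignores baseline altogether. The text does not settle this. Measuring before and after fits a change score, which does use baseline, and the full protocol or analysis plan may define the outcome. What remains is that neither reading gives a covariate-adjusted test or estimate.

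The size of the gain rests on two figures absent from the article. The fall to 64% on change scores is not a property of the plan: it needs both ρ = 0.3 and 7.3 as the SD at each visit, and Step 4 removes it. That baseline explains much of the follow-up variance is not documented either; at ρ = 0.3 it explains 0.3² = 9%. Entry requires a Fatigue Severity Scale score of at least 4, which may narrow the baseline range and lower ρ.

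The simulations use normal data, which the article does not expect. They cover the three-group test only, not pairwise contrasts at the article's 0.017 threshold. Both limits stand.

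Finally, this is a feasibility pilot whose primary endpoint is stimulation time, which this point does not touch. BDI, SF-36 and PCS are called descriptive, so a power argument has little force for them.

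**Conclusion.** The point holds as a matter of efficiency. The article fixes tests and estimates without a baseline covariate, leaves open whether week-4 or change scores are ranked, and collects the baseline that would sharpen the MFI20 comparison.

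With an SD of 7.3 at each visit and ρ of 0.3/0.5/0.7, rank ANCOVA gains about 2, 9 and 17 points over the week-4 test, and about 18, 9 and 1 over the change-score test. If 7.3 is the SD of change, the difference from the change-score test runs from about +13 points at ρ = 0.3 to about −1 at ρ = 0.8. It would therefore be too strong to call adjustment free: there is no gain over the week-4 test at ρ = 0, and about one point or less may be lost against change scores at ρ = 0.8. All these figures assume normal data and an SD and correlation that the article does not give.

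The change is worth making, but the trial does not depend on it. The power argument is confined to MFI20; for the other questionnaires the benefit is precision of the reported differences.

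**What to change.** Specify that Visit 1 MFI20 is analysed by rank analysis of covariance (Quade's method) with baseline MFI20 as covariate, for both the three-group test and the pairwise contrasts. Report baseline-adjusted mean differences with 95% confidence intervals in place of the raw ones. Keep Kruskal-Wallis and the Hodges-Lehmann shift as supportive, and state whether they use the week-4 score or the change. Apply the same adjustment to the BDI, SF-36 and PCS estimates for precision, without a power claim.

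The cost is about one sentence of analysis wording and, in the least favourable case examined, about one point of power. No extra patients, visits or data are needed. Quade's method is rank-based, so the article's reason for choosing ranks is still met.

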### Study plan (Fig 1)

#### Verum stimulation.

This study included two verum-stimulation groups. In both groups, taVNS will be administered according to the device approval at the cymba conchae of the left ear. Because establishing a placebo group in stimulation studies is generally difficult, two Verum groups were planned: one will receive stimulation above the sensory threshold, and one below. If subthreshold stimulation also leads to a positive effect, future studies may omit the suprathreshold stimulation group.

**Fig 1 pone.0315606.g001:**
[figure not shown]
SPIRIT schedule of enrollment of the CoViva Study.

Stimulation will be conducted using the commonly chosen parameters in the literature, which have been successfully applied over a period of 20 weeks [54]. These parameters include a frequency of 25 Hz and a pulse width of 250 µs. These stimulation parameters will be preset in the commercially available, CE (Conformité Européenne, European equivalent to FDA) tVNS-L stimulator and cannot be changed. Stimulation will be applied throughout the day for 4 h using a 28s on/ 32s on/off schedule. Patients will be asked to download available Android and iOS apps, which will be paired with the stimulator via Bluetooth to document the daily stimulation time. Based on these records, patients will be able track when the recommended 4 h daily stimulation target day is reached. Although the stimulator will be turned off after 4 h of continuous stimulation, there is no automatic blocking of the stimulator after 4 h of cumulative stimulation, as only patients who understood the study protocol will participate, in accordance with the exclusion criteria. Additional negative effects of a stimulation lasting more than 4 hours have not been reported in literature – however, the likelihood of known side effects such as headache, ear pain, skin irritation or nausea [55] increases if stimulation lasts longer than 60min [56].

#### Verum-1 stimulation.

The intensity will initially be set to produce a mild tingling sensation in the ear that should not be painful. Subsequently, the intensity will be reduced to a level at which the patient no longer feels the stimulation. The patient will then be asked to repeat this procedure every time stimulation is initiated to ensure that the stimulation is always subthreshold.

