### Selection of patients and data collection

A total of 45 patients will be recruited and divided into three groups. Patients will be informed about the study through flyers and by their general practitioners, and will be provided with access to a website. Additionally, local support groups will be contacted and informed. On the website, questions regarding the inclusion and exclusion criteria will be asked anonymously, without data storage. At the end of the questionnaire, patients will be informed of whether they qualified for the study. In the case of study qualifications, patients will be provided with an email address where they can sign up to participate. Patients will be informed about the study aims and procedures by an investigator or certified medical professional. After obtaining written informed consent, data collection will be pseudonymized in the RedCap electronic case report form (eCRF) system of Ruhr-University-Bochum and will be General Data Protection Regulation (GDPR)-compliant. The RedCap system automatically randomizes patients into Verum-1, Verum-2, or Sham groups (n = 15 each). The patients will be instructed on how to use the simulator for 4 h per day, with at least 1 h of consecutive stimulation in the left ear. Patients will be asked to log all stimulation times manually in a diary. Because patients in the sham group will also receive the device’s user manual, which states that they should feel a tingling sensation in the ear, they will be instructed to use the highest stimulation intensity that is not perceptible to them. After adjusting the stimulation to this level, sham patients will receive a non-functional electrode that does not perform any stimulation. This approach is justified as the principle “more is better” does not apply to vagus nerve stimulation, and stimulation below the perception threshold could still, theoretically, have an effect.

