#### Sham stimulation.

The intensity will initially be set to produce a mild tingling sensation in the ear that should not be painful. Subsequently, the intensity will be reduced to a level at which the patient no longer feels any stimulation. The stimulator will be maintained at this level throughout the study. However, participants in the sham group will receive an ear electrode provided by the manufacturer, which is based on a regular electrode but does not establish an electrical connection between the stimulator and ear contact, ensuring no actual stimulation occurs.

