### Sham intervention

Defining the sham group in a stimulation study is challenging. Several different approaches have been discussed in the literature, including stimulation of the ear lobe instead of the cymba conchae, or stimulation of other parts of the body [63–66]. However, an informed patient may realize that such stimulation is different from normal taVNS, and could thus identify themselves as being in the sham group. To address this, patients will alternately provide with information that they will either feel or do not feel the stimulation. Once the tingling sensation has been demonstrated to the patient, the intensity will be reduced until the patient does not feel any stimulus. The sham group will then be provided with a non-functional electrode, while the verum-1-group will maintain their functional electrode throughout the study phase. If the analysis shows that both the verum-1 and verum-2 interventions have a significant effect on fatigue, future studies will need only one subthreshold group and one sham group, leaving the patients blinded to which group they have been included in.

Within this feasibility trial, no invasive procedures, such as blood sampling, has been planned, in order to maintain the regulatory requirements as low as possible. The stimulation system tVNS-L® is manufactured by tVNS GmbH in Erlangen, Germany. This system allows modification of the stimulation intensity but not of the pulse width or frequency. As such, it is a CE-mark for transcutaneous auricular vagal nerve stimulation. The variant tVNS-R® (R for research) allows modification of all parameters; consequently, it does not have a CE-mark, making it extremely difficult to obtain insurance and ethical approval for a scientific study.

The results of this study will be published in scientific, probably open-access, journals with a scope for public health. If taVNS, as a very safe procedure, can improve fatigue and the challenging sequelae of long covid, it would significantly improve the quality of life of such patients. This potential improvement in the quality of life justifies the extremely low risk of taVNS therapy in this study.

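### Masking of sham against Verum-1, the only pair of arms that could be masked, cannot be relied on, because take-home handling differs and the patient information is inconsistent

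*Protocol article*

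**What the plan says.** All places are in the protocol article.

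- **Verum-1 stimulation.** Intensity is raised to a mild tingling and then lowered until nothing is felt. At home, "The patient will then be asked to repeat this procedure every time stimulation is initiated", with the aim of keeping it below threshold.
- **Sham stimulation.** The initial setting is the same, but afterwards "The stimulator will be maintained at this level throughout the study". The sham electrode "does not establish an electrical connection between the stimulator and ear contact".
- **Selection of patients and data collection.** Sham patients hold the device manual, which tells them to expect tingling. For that reason they are told to use the highest level they cannot perceive. The order of events is: "After adjusting the stimulation to this level, sham patients will receive a non-functional electrode that does not perform any stimulation".
- **Verum-2 stimulation.** The patient keeps the intensity above the sensory threshold, so the stimulation is felt.
- **Abstract.** Patients are randomised to the three arms "after being informed that they will feel the stimulation".
- **Sham intervention (Discussion).** Other sham methods are set aside because an informed patient might recognise them. As the answer to this, "patients will alternately provide with information that they will either feel or do not feel the stimulation", and "The sham group will then be provided with a non-functional electrode, while the verum-1-group will maintain their functional electrode throughout the study phase".

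The Verum stimulation and Sham intervention sections both say that the results for the verum arms will inform which arms future studies keep.

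**The concern.** The method under Sham intervention works only if a sham patient and a Verum-1 patient have the same experience: one demonstration of tingling, then nothing felt. The arm descriptions do not deliver that. One arm handles the intensity control and feels a live electrode at every start. The other is left at a fixed setting on a dead electrode. The document also does not settle what patients are told to expect.

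MFI20, BDI, SF36 and the PCS score are all patient questionnaires, so a difference in belief about the device can move them. Usage time, on which the primary endpoint rests, is behaviour. An added step at each start, or a suspicion that the device is dead, could change it. At stake is the reading of the sub-threshold contrast, which the article would use to decide whether a later trial needs a supra-threshold arm at all.

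**Working it through.** No arithmetic decides this point. It was checked by setting the sections side by side.

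**Step 1: which pair could be masked.** Verum-2 is perceptible throughout, so no contrast involving it can be patient-blinded. That leaves Verum-1 versus sham.

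**Step 2: handling of that pair.**

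| | Verum-1 | Sham |
|---|---|---|
| Demonstration at Visit 0 | tingling felt, then lowered | tingling felt, then lowered |
| Electrode afterwards | functional | no electrical connection |
| At each home start | go up to tingling, come down again | level left as set |
| Evidence of a live device after Visit 0 | at every start | none |

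The first row matches. The other three do not. The electrode difference is the intended treatment difference. The last two rows are differences in procedure and in what the patient learns.

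**Step 3: two ways a sham patient may behave.**

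- *The level is never touched*, as under Sham stimulation. The patient may remain masked, but the arms still differ in handling, and only Verum-1 patients confirm a working electrode.
- *The intensity is raised*, for example to find again the highest level that cannot be felt, or to look for the tingling the manual describes. Nothing is felt at any setting, although tingling was felt at Visit 0. A patient who knows that a sham arm exists (an assumption, since the consent text is not shown) can infer the allocation.

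The arms are unequal in either case. In the second, the sham patient can also be unmasked.

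**Step 4: patient information.**

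- Abstract: all patients are told they will feel it.
- Sham intervention: patients are told either that they will or that they will not.
- Selection of patients and data collection: sham patients are told to use a level they cannot perceive.

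The second and third statements are compatible. The Abstract fits neither.

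**Step 5: size.** The Sample size calculation section assumes a Verum-1 advantage of at least 5 MFI units over placebo. The document gives no figure for an expectation effect on the MFI20, so there is nothing to set against those 5 units.

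**The case against.** The strongest case on the other side has five parts.

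- **The trial is never called patient-blinded.** This is correct. The one sentence that speaks of blinded patients concerns future studies. A reader might infer that the article promises a blinded comparison here and breaks the promise, and the text does not support that. It does support a masking aim: the Sham intervention section names the risk that patients recognise sham and offers this trial's method as the answer.
- **Unmasking is not shown to occur.** Also correct. Patients see only their own arm, and a sham patient who leaves the control alone feels what the instruction led them to expect. A reader might conclude that the contrast is unblinded. The documents support only that its masking cannot be relied on.
- **The manual problem is already recognised.** This is true. The imperceptible-level instruction is the article's own response to the manual. It does not help a sham patient who turns the intensity up.
- **The number of live-device confirmations is unknown.** One start on every day for 4 weeks would give 4 × 7 = 28 in Verum-1, and it is tempting to call that a minimum. It is not, because it presumes daily use, and actual use is what the primary endpoint measures. It is likewise tempting to say that an expectation effect of a few MFI units would mimic the assumed 5, but no such effect is given in the document.
- **This is a feasibility pilot of 45 patients with acceptance as the primary endpoint.** This stands as a limit on the consequences, which fall mainly on secondary outcomes. It does not remove the point, because the article would use those outcomes to choose future arms.

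**Conclusion.** The point holds in this form: masking of sham versus Verum-1 cannot be relied on. The arm descriptions, followed as written, give the two sub-threshold groups unequal handling and unequal evidence of a working device. The Abstract's statement on patient information contradicts two later sections. This is a matter of what the article states, not of detail left to a fuller document.

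The consequence is possible bias, of unknown size, in the MFI20, BDI, SF36 and PCS comparisons between Verum-1 and sham, and possibly in usage time. Verum-2 contrasts are not patient-blinded in any case, so no efficacy contrast in the trial is securely free of expectation effects.

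The conclusion rests on two assumptions. One is that the masking aim under Sham intervention applies to this trial, which is inferred from the text. The other is that patients know a sham arm exists. The second is needed only for a patient to infer the allocation; the difference in handling does not depend on it.

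**What to change.** 1. Reconcile the Abstract, Selection of patients and data collection, Verum-1 stimulation, Sham stimulation and Sham intervention sections, so that the take-home instructions and patient information for the two sub-threshold arms agree with each other and with the stated masking aim. Which intensity procedure to use is for the clinical team, and this review does not propose one.
2. Add one item to the Visit 1 eCRF that asks patients which arm they believe they were in.
3. Flag patients already treated under the present instructions. The study began on 1 September 2023, so there may be some.
4. State in the Data analysis section that contrasts with Verum-2 are not patient-blinded, and that Verum-1 versus sham efficacy results will be read in light of the treatment-guess data.

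The cost is revised instruction and protocol wording and one eCRF item. The sample size and the planned tests do not change.
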